### Handling of Missing Data

Given the advanced age and varying functional capacity of participants, some degree of missing data is anticipated. The extent and pattern of missing responses will be examined descriptively. If item-level missingness exceeds 10%, this will be analyzed to determine whether it reflects systematic difficulties (eg, item wording, administration mode, or functional limitations). In CTT analyses, cases with excessive missing responses may be excluded from specific analyses. In RMT, the model accommodates some degree of missing data under the assumption of conditional independence; however, patterns of missingness will be evaluated to ensure that they do not reflect systematic bias.

### Ethical Considerations

The PLAY-SE program is conducted in accordance with the ethical principles for research involving human subjects, as outlined by the Swedish Ethical Review Authority. Ethical considerations are made throughout the research program, in accordance with the Swedish Ethical Review Act [59] and the Declaration of Helsinki [60]. Ethical approval has been obtained for the qualitative work in phase 1 (registration number 2025-00211-01). A complementary application will be submitted before data collection for later milestones. All data will be handled in accordance with established ethical standards for privacy and confidentiality. No identifying information (eg, names, initials, or other personal identifiers) will be included in the manuscript or supplementary materials. No compensation will be offered to participants.

Participation is voluntary and based on informed consent. Only older adults capable of providing informed consent will be included, and participants may withdraw at any time without consequence. As participants are older adults receiving municipal care, they may constitute a potentially vulnerable group due to age-related functional limitations and dependency structures.

To minimize risks and safeguard voluntariness, several measures are implemented. Recruitment is facilitated by designated care staff to identify eligible individuals; however, study information, eligibility confirmation, and informed consent are handled directly by the research team to emphasize independence from care provision. Participants are explicitly informed that participation or nonparticipation will not influence their care in any way.

Participants choose the time and location of interviews to ensure a familiar and secure setting. Focus groups are conducted separately for managers and staff to reduce power imbalances. During questionnaire administration, staff will not be present unless necessary for practical support. Any assistance provided follows a standardized protocol limited to reading items aloud and recording responses without interpretation. Given the risk of social desirability bias in care contexts, mode of administration (independent vs assisted completion) will be documented and examined analytically through DIF testing.

As discussions about playfulness may evoke emotional responses, participants are offered follow-up contact if needed. Confidentiality is emphasized throughout, and all research data are pseudonymized or anonymized as appropriate, securely stored, and managed in accordance with applicable data protection regulations and institutional policies.

A reference group of older adults has been involved from the outset and remains engaged throughout the research process. This participatory approach supports the ethical commitment to treating participants as situated knowers and strengthens the contextual sensitivity of instrument development.

Findings from the PLAY-SE program will be disseminated through publication in peer-reviewed journals and presentation at national and international conferences. Summaries will be prepared for practitioners and older adults and shared with participating care units and municipal stakeholders to facilitate knowledge translation into practice.

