### Initial Conceptualization and Theoretical Hierarchy

As part of this review and study protocol, an initial conceptualization and theoretical hierarchy for the PLAY-SE instrument were developed. This process drew on insights from the literature, together with conceptual reasoning, providing a theoretically grounded basis for the forthcoming item generation and psychometric evaluation. The conceptualization and hierarchy will be further elaborated in forthcoming discussions within the research team, drawing on findings from phase 1 and serving as a springboard for phase 2 of the program. The PLAY-SE will be a self-administered instrument comprising approximately 25 statements across 6 preliminary conceptual domains: : “Across the Life Course,” “Attitudes,” “Environment and Enablers,” “Emotional Meaning,” “Health and Well-being,” and “Playful Activity.” While designed for independent completion, support from staff should be offered, if needed, to ensure that all participants can engage with the instrument on their own terms. Higher scores will reflect greater levels of playfulness or engagement in play among older adults receiving municipal care (Figure 2).

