4. Environment and enablers	Captures how the environment and the body influence the possibility of engaging in play.	Reflects a willingness to play, acknowledging that expression depends on external conditions such as physical ability, institutional rules, or support.
5. Across the life course	Measures self-image and the continuity of playfulness throughout the lifespan.	Requires a stronger personal anchoring, as identifying oneself as playful over time implies a deeper integration of playfulness into one’s identity.
6. Playful activity	Captures behavioral expressions of play.	The most demanding domain reflects concrete engagement in playful actions and the creation of playful situations, indicating the highest level of expressed playfulness.

The 6 proposed domains for the PLAY-SE instrument are specifically designed to bridge older adults’ lived experiences with complex theoretical perspectives (such as person-centered care, lifeworld theory, and existential philosophy) by translating abstract concepts into dimensions that are both measurable and meaningful to the individual in their context. The domains collectively ensure that the instrument does the following:

Centers the person and their subjective meanings (person-centeredness). Mainly captured by the domains of *attitudes* (toward play) and *emotional meaning*, which reflect personal values, emotional relevance, and how individuals perceive the role of play in their own lives.Reflects the totality of human experience—body, time, space, emotion, and sociality (lifeworld theory). Mainly captured by *environment and enablers*, *across the life course*, and *health and well-being,* which together address the spatial, temporal, emotional, physical, and social or intersubjective aspects of being playful in everyday life.Accounts for existential challenges and choices, such as freedom, limitation, loss, and identity (existential philosophy). Mainly captured by *playful activity*, *emotional meaning*, and *across the life course*, which reflect the tension between agency and constraint, the significance of loss, and the continuity of identity through play.

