### Administration Procedures and Mode Effects

The PLAY-SE instrument is designed for self-administration. However, given the target population, some participants may require assistance (eg, due to visual impairment or motor limitations). To ensure procedural consistency, assistance will follow a standardized protocol. Support will be limited to reading items aloud and recording responses as expressed by the participant, without interpretation, rephrasing, or prompting. The mode of administration (independent completion vs assisted completion) will be documented for each participant. This variable will be included in subsequent psychometric analyses.

Potential mode effects will be examined analytically. In the Rasch analysis, DIF will be tested across administration modes to determine whether assisted completion systematically influences item responses. If significant DIF is identified, its impact on measurement invariance will be evaluated.

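### Care staff may read items aloud and record answers for participants who need help, and the independent/assisted code cannot show later which answers were given to care staff

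*Protocol article*

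**What the plan says.** Four places in the Protocol article bear on this.

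- **Ethical Considerations** describes participants as potentially vulnerable, partly through dependency, and names social desirability in care contexts as a risk. It gives consent to the research team so that it is independent of care. For the questionnaire it says: "During questionnaire administration, staff will not be present unless necessary for practical support". It then defines the help: "Any assistance provided follows a standardized protocol limited to reading items aloud and recording responses without interpretation".
- **Initial Conceptualization and Theoretical Hierarchy** says who gives the help: "support from staff should be offered, if needed, to ensure that all participants can engage with the instrument on their own terms".
- **Administration Procedures and Mode Effects** says who may need it: "some participants may require assistance (eg, due to visual impairment or motor limitations"). It bars the helper from interpreting, rephrasing or prompting, and fixes the record: "The mode of administration (independent completion vs assisted completion) will be documented for each participant". Differential item functioning (DIF) is to be tested across these two modes.
- **Table 1, domain 4 (Environment and enablers)** describes content in which "expression depends on external conditions such as physical ability, institutional rules, or support".

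**The concern.** Keeping staff away is the plan's own protection against answers shaped by dependency. It lapses when a participant cannot complete the form alone, and the reasons given for needing help (sight, motor function) are also reasons for relying on care staff. The rules on how to help govern what the helper says. They do not change the fact that the helper hears and writes down each answer.

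Two things are at stake. Answers on rules and support may be less candid when given to someone who provides that support, and the Protocol article presents environmental enablers and constraints as part of what distinguishes PLAY-SE from trait scales. In addition, one assisted level merges help from the participant's own carers with help from other staff or the research team. If helper role is not recorded at the time, no later analysis can recover it.

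**Working it through.** The plan gives no figure to reproduce. The main check is to read the passages together; the arithmetic after it is illustrative.

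**Reading the passages together**

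1. Staff are absent unless practical support is needed (Ethical Considerations).
2. Assistance means reading items aloud and recording the replies (same section, and Administration Procedures and Mode Effects). Whoever helps therefore knows the answers.
3. Staff are to offer the support (Initial Conceptualization and Theoretical Hierarchy). Ethical Considerations treats care staff and the research team as separate groups. No section gives the helping task to the research team or excludes the participant's own carers.
4. The stated record is independent or assisted. Helper role is not part of it.

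So own-carer help is permitted, and the stated variable would not show where it happened.

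**How many people and items**

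Inputs: validation sample 250 to 500 (Setting and Participants); about 25 items (Initial Conceptualization and Theoretical Hierarchy); about 3 to 5 items per domain (Item Generation and Content Development). The assisted share is assumed to be 20% to 40%.

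- Assisted participants: 0.20 × 250 = 50, up to 0.40 × 500 = 200. This counts people helped by anyone.
- Environment domain: 3/25 = 12% to 5/25 = 20% of items.

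**What pooling the helpers costs**

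All effect inputs here are assumptions: help from care staff shifts one item by 0.5 SD, other help shifts it by nothing, and half of assisted participants are helped by care staff. Two-sided alpha is Bonferroni-adjusted over 25 items, 0.05/25 = 0.002, so z = 3.09. With group sizes n1 and n2 and standardised difference d:

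power ≈ Φ( d × √[n1·n2/(n1+n2)] − 3.09 )

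Under the two-level code the difference is diluted to 0.5 × 0.5 = 0.25 SD. With helper role recorded, staff-assisted participants are compared with independent ones at the full 0.5 SD but with half as many assisted people.

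| N | Assisted share | Two-level code: n1 vs n2, power | Helper role recorded: n1 vs n2, power |
|---|---|---|---|
| 250 | 20% | 200 vs 50, 0.07 | 200 vs 25, 0.23 |
| 250 | 40% | 150 vs 100, 0.12 | 150 vs 50, 0.49 |
| 500 | 20% | 400 vs 100, 0.20 | 400 vs 50, 0.60 |
| 500 | 40% | 300 vs 200, 0.36 | 300 vs 100, 0.89 |

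Worked example, last row: √(300·200/500) = 10.95; 0.25 × 10.95 − 3.09 = −0.35, so power is 0.36. With helper role, √(300·100/400) = 8.66; 0.5 × 8.66 − 3.09 = 1.24, so power is 0.89.

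The gain depends on the helper mix. If a quarter of helpers are care staff, power is 0.01 to 0.04 pooled and 0.08 to 0.57 separated. If all are care staff, the two codes give the same power (0.53 to 0.78 at N = 250, 0.92 to 0.99 at N = 500).

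**The case against.** The strongest reply is that the Protocol article is a condensed account. It refers to a standardized assistance protocol that is not shown, and a complementary ethics application is still to come before the pilot. Either could name the helper or add a field, and recording independent or assisted does not forbid recording more. That stands as a reason for moderation. It does not remove the point, because the article itself states the staff support, the exception and the two-level variable.

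Other replies also carry weight:

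- *Own carers are not named.* Correct. A reader might infer that assisted participants always answer to the staff who care for them. The text says only staff, undefined, so this is a possibility.
- *If all helpers are staff, the code already identifies staff help.* Partly. It would still not separate the participant's own carers from other staff.
- *Phase 2 recruits mainly in ordinary housing* (Sampling Strategy). This weakens any picture of residents judging their own unit. Residential care stays in the program, and for people at home the dependency is on the home-care service.
- *The environment domain is not a rating of staff.* Fair. Its items are unwritten and it also covers bodily ability, so withheld criticism is a risk and has not been shown.
- *Safeguards remain.* Help is restricted to reading and recording, participants are told that taking part or not will not affect care, mode is documented and tested for DIF, and mode is one explanation examined when item missingness exceeds 10%. A reader might infer that protection is wholly absent; it is not. These steps do not make the answers private from the helper, and they cannot isolate help from care staff.

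**Conclusion.** The point holds as a cheap improvement to a stated method. The plan permits care staff, possibly the participant's own carers, to hear and record the answers of participants who need help, although it names dependency and social desirability as risks and otherwise keeps staff away. The two-level record then makes those answers inseparable from other assisted answers.

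The size is uncertain. The 50 to 200 assisted participants rest on an assumed 20% to 40% share and count help from anyone; the own-carer part could be anywhere from near none to all. The power figures rest on an assumed effect and helper mix and only illustrate the cost of pooling. The documents do not support saying that own-carer help always occurs, that answers about rules or support will be withheld, or that participants who need help have no protection.

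**What to change.** 1. In Administration Procedures and Mode Effects and in Ethical Considerations, replace independent/assisted with helper role: none; staff who give this participant care; other staff; research team; other. The planned two-level contrast can still be derived from it.
2. In Initial Conceptualization and Theoretical Hierarchy and in Ethical Considerations, state that, where existing staffing allows, the helper is not someone who provides that participant's care.
3. Report the mode/DIF analysis and the environment domain with and without participants helped by their own care staff, collapsing helper categories where cells are small.

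The cost is one extra coded field and some scheduling, best settled before the pilot planned for autumn 2026 and in the pending ethics application. The downside is small cells: with 50 assisted participants, half of them helped by care staff, the key group has 25 people. Helper role will also not separate a helper effect from the functional limitation that made help necessary. Requiring research-team helpers throughout could need extra staff, so a stated preference is enough. Having participants mark answers out of the helper's sight is not proposed, because many who need help for visual or motor reasons could not do it.

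### DIF by administration mode detects only item-specific effects and mode follows need for help, so the stated check can neither rule out social desirability bias nor attribute it to assistance

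*Protocol article*

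**What the plan says.** Administration Procedures and Mode Effects (Methods) states the purpose of the test: "DIF will be tested across administration modes to determine whether assisted completion systematically influences item responses". If DIF appears, the next step is "If significant DIF is identified, its impact on measurement invariance will be evaluated". The same section says of the mode variable: "This variable will be included in subsequent psychometric analyses", without saying how.

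Ethical Considerations links the test to a named bias: "Given the risk of social desirability bias in care contexts, mode of administration (independent vs assisted completion) will be documented and examined analytically". The same sentence names DIF testing as the means.

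Table 2 (Prespecified Psychometric Criteria) fixes the method: a two-way ANOVA on Rasch residuals, judged after Bonferroni adjustment, with an item split to be considered if the result is significant.

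Mode is not assigned by design: "some participants may require assistance (eg, due to visual impairment or motor limitations"). Initial Conceptualization and Theoretical Hierarchy adds that "support from staff should be offered, if needed".

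There are also procedural safeguards. Help is limited to reading items aloud and recording answers, and "staff will not be present unless necessary for practical support".

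**The concern.** The article expects the DIF test to establish whether assistance systematically influences responses, and offers that test as the analytic answer to social desirability. Two features of the test stand in the way.

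- **Blindness to a common shift.** A DIF test asks whether people with the same person measure answer an item differently in the two modes. A general tendency to answer more favourably changes the person measure itself, so nothing is left for the test to find.
- **No attribution.** People are helped because they have limitations. The Environment and enablers domain in Table 1 asks how the environment and the body affect play, so impairment alone could produce different responses to those items. A flagged item could reflect either cause.

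The stake is how the validation results can be read. Scores are to be related to the SMAP and to well-being indicators, and the program aims at invariant measurement. A nonsignificant DIF result would not show that assisted scores are free of inflation. A significant one, followed by an item split, could adjust away a difference that belongs to the construct.

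**Working it through.** The article gives no calculation for DIF by mode, so there is no figure to reproduce.

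**Inputs from the article.** About 25 items; 250 to 500 participants in the validation study; two-way ANOVA on residuals with Bonferroni adjustment.

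**Assumptions not in the article.** Base alpha 0.05; two tests per item (uniform and non-uniform DIF); four response categories; person SD 1 logit; 30% assisted; the sizes of the bias.

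**Step 1: the identity.** In the Rasch model the logit for person n on item i is theta_n − beta_i. If assistance adds c to every item, the logit is (theta_n + c) − beta_i. These data have the same distribution as data from a person whose true location is theta_n + c. The estimated person measure absorbs c, and residuals conditional on it carry no mode effect. Sample size plays no part in this.

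**Step 2: simulation.** The setting was 25 rating-scale Rasch items, a residual ANOVA with five class intervals by mode, per-test alpha 0.05 / (2 × 25) = 0.001, and 200 datasets per cell.

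| Scenario for assisted respondents | Any item flagged, N = 250 | Any item flagged, N = 500 | Mean difference in person measure (logits), N = 250 / 500 |
|---|---|---|---|
| No bias | 4.0% | 4.0% | 0.02 / 0.00 |
| +0.5 on every item | 5.0% | 9.5% | 0.53 / 0.52 |
| +1.0 on every item | 6.5% | 5.0% | 1.06 / 1.06 |
| +0.5 on every item, true level 0.5 lower | 8.0% | 5.5% | 0.02 / 0.00 |
| +1.0 and 0 on alternate items (about +0.5 on average) | 100% | 100% | 0.50 / 0.53 |
| +0.8 on 7 of 25 items | 98.5% | 100% | 0.21 / 0.21 |

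The Monte Carlo standard error at a 5% rate is √(0.05 × 0.95 / 200) = 1.5 percentage points. The 9.5% cell lies above 5% by more than that noise easily explains. But doubling the shift at the same N gave 5.0%, so detection does not grow with the bias. A separate simulation with four class intervals, 10% to 30% assisted and a common +0.5 shift gave flag rates of 3% to 7%.

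**Step 3: what item-varying bias shows.** The last two rows show that uneven bias is found. In the alternating scenario an average of 5.7 items (N = 250) and 15.7 items (N = 500) were flagged. The average inflation of about 0.5 logit is still not measured by the DIF test.

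**Step 4: would comparing person measures help?** An unadjusted t test of mean person measures by mode detected the common +0.5 shift in 92.5% (N = 250) and 99.5% (N = 500) of datasets. When assisted people were truly 0.5 logit lower, the two effects cancelled and detection fell to 5.0% and 6.5%. The comparison therefore adds information that DIF lacks, but needs adjustment for limitation and remains open to residual confounding.

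**Step 5: a further limit.** Social desirability present to the same degree in both modes cannot appear in any comparison by mode.

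**The case against.** The strongest reply has four parts.

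- **Uniform bias is a special case.** The six domains run from general opinions to concrete behaviour, so desirability pressure could well differ between items, and uneven bias is almost always flagged under the assumptions above. This stands. A reader might infer that the bias would go undetected altogether; the documents and the calculation do not support that. Only the common component is invisible. Nor does confounding hide DIF; it limits what a flag means.
- **The mode variable will be used more widely, and details may sit in a fuller plan.** Possible. But the article itself says what the DIF test will determine, and that statement is wrong for a common shift whatever else is planned.
- **Procedure is the main protection.** Restricting help to reading and recording, and keeping staff away where possible, may well reduce the bias. It does not enable the DIF test to show whether bias remains.
- **The size is assumed.** This stands. Putting in 0.5 logit and recovering about 0.5 logit illustrates the identity; it does not estimate bias in this study.

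A reader might also infer that care staff will act as helpers while respondents rate those staff's own support. The article does not say who will help during data collection, and the items are not yet written, so this is not part of the point. Likewise, no passage says that a clean DIF table will be reported as absence of bias, or that DIF will be blamed on assistance.

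**Conclusion.** The point holds in a limited form. The only specified analytic check for social desirability detects item-specific mode effects and has essentially no power against a shift common to all items. That rests on the form of the Rasch model and not on the assumed shift size, assisted share or sample size. The percentages do rest on those assumptions and should be read as illustration only. Because mode follows need for help, a difference that is found cannot be attributed to assistance rather than impairment. The check can therefore neither rule the bias out nor attribute it.

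This is a should-fix. It concerns an overstated claim and a missing companion analysis in an instrument-development study; it does not undermine the design, and the remedy is small.

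**What to change.** 1. In Administration Procedures and Mode Effects and in Ethical Considerations, state that DIF by mode tests item-specific effects only. Replace the claim to determine systematic influence with wording about association between mode and item responses.
2. Add a comparison of mean person measures by mode with a confidence interval, adjusted for age, care setting and the reason for assistance. The article does not say that this reason is recorded, so it needs one added form field. The field should record the relevant limitation (visual, motor, other) for every participant, because a reason asked only of assisted people coincides with mode and cannot serve as a covariate. State that residual confounding remains.
3. Repeat the main psychometric and validity results in independent completers as a sensitivity analysis, noting that this selects less impaired respondents.

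Recording who gave the help is optional.

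The cost is one form field, one regression, one repeated set of analyses and a few changed sentences. The field has to be in place before collection. The pilot is planned for autumn 2026 and the complementary ethics application is described as still to be submitted, so it can be included there.
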